### Study endpoints

The *primary* endpoint of the study is the *feasibility* of the combined intervention as assessed at the post-intervention visit (V4), except in case of compensation sessions, where *feasibility* will be assessed at the end of treatment. To test *feasibility*, we use the following quantitative definition: the intervention is feasible if the probability of a study participant to successfully apply a number of at least 20 out of 30 sessions per protocol exceeds 50%, i.e., it is more likely to receive an adequate dosage of treatment sessions. The threshold of 20 out of 30 treatment sessions is largely based on previous trials of tDCS in MDD, i.e., being close to the tDCS session number in the ELECT TDCS trial and at a higher number of sessions compared to the SELECT trial (22 sessions and 12 sessions, respectively; [26, 27]) to prevent an insufficient dosage of the intervention in this trial. To test this hypothesis, we will determine the quotient of participants successfully completing the intervention according to this criterion relative to the total number of participants. This endpoint was chosen as the primary endpoint due to the novelty of our study design, in which the treatment is performed mostly in a home-based setting. The study has been powered to examine feasibility in the whole sample (i.e., both treatment arms together). In a second step we will estimate confidence intervals for each of the treatment arms separately.

The secondary endpoint is *efficacy,* measured as the change in *MADRS* scores from the baseline visit (V1) to the post-intervention visit (V4). Tertiary endpoints include *clinical response* (at least 50% reduction in the MADRS score from baseline), *remission rates* (MADRS score ≤ 10 points), and *depression relevant status,* assessed via changes in depressive and functional outcomes. Changes on all other assessments from baseline to post-treatment, including *QoL, rumination*, and *cognitive control functions* including *multitasking*, *inhibitory control* as well as *sustained attention* are also included as *tertiary* endpoints*.*

*Exploratory* endpoints include *durability of effects* (i.e., changes on all measures between baseline and follow-up), *expectation for treatment effects* (CEQ scale), *motivation* to participate in the game (IMI scale), and additional domains of cognitive control including the assessment of *WM capacity* and *task switching*.

### Randomization and blinding

Participants are randomized to receive either active or control treatment following a parallel group assignment. Randomization is performed separately for each site. Patient allocation is stratified by the magnitude of the MADRS score (MADRS < 21.5 vs. MADRS ≥ 21.5). No other stratifiers are used to conserve statistical power. Within stratification, allocation is balanced in groups of four. Randomization is centrally performed by the coordinating site (HUJI) using an online randomization tool (Randomizer; https://www.randomizer.at).

Double-blinded treatment is implemented to minimize bias during the data assessment driven by potential expectation biases of raters and/or patients. Separate study personnel are responsible for the study assessments (*raters, i.e., blinded investigators*) as compared to the implementation and supervision of the treatment (*unblinded investigators* including *study operators*). Raters and patients are blind to the administered treatment condition. Raters are not in direct contact with the patients during the treatment sessions. Patients are asked to refrain from talking about their treatment (apart from experienced AEs) with the raters. Study participants are required to refrain from meeting each other before, during, and after assessments or treatments to maintain blindness. A *blinding check* is performed after the first treatment and after six weeks of intervention (V4), in which patients are asked whether they believe that they were assigned to the active or to the control condition.

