### Study sites

The clinical trial is conducted at the following study sites: (1) Department of Psychiatry and Narcology, Riga Stradins University (RSU), Riga, Latvia (PI: [name], MD), (2) Department of Psychiatry, Hadassah Medical School, Hebrew University, Jerusalem, Israel (PI: [name], MD), and (3) Department of Psychiatry and Psychotherapy, University Hospital, LMU Munich, Germany (PI: [name], MD). The trial is coordinated and monitored centrally by the coordinating study site (HUJI; PI: [name]), supported by the co-coordinating study site (LMU; PI: [name]).

The three clinical trial sites are in charge of patient recruitment, patient screening, data assessment, and implementation of the intervention. For this purpose, the sites are equipped with the treatment set-up and with comprehensive training materials, including manuals, instruction videos, and standardized operation procedures (SOPs). *Study operators* and *unblinded investigators* were trained for the use of the treatment device including its preparation, implementation, and dismantling. Their training included control of the integrated gaming and stimulation software including the correct use of the algorithm-controlled application for facilitated electrode positioning, on-site patient teaching of proper equipment handling, direct supervision of on-site treatment and remote supervision of home-treatment, as well as comprehensive and adaptively extended troubleshooting protocols. *Raters* (*blinded investigators*) underwent assessment training. Both unblinded investigators and raters were trained on how to use the electronic database.

Ongoing scientific and technological support during the trial is provided by the following project collaborators: Faculty of Psychology and Education Sciences, University of Geneva (UNIGE), Geneva, Switzerland (PI: [name]) and Faculty of Medicine, Hebrew University of Jerusalem (HUJI), Jerusalem, Israel (PI: [name]) for the use of the LoH and LoH_control video games; Ecole Polytechnique Fédérale de Lausanne (EPFL), Switzerland (PI: [name]) for the use of the tDCS device and the algorithm-controlled electrode positioning software. Additional technical support for the use of the tDCS device is given by the support team of Neuroelectrics Inc..

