### Sample size calculation

Sample size was determined based on the feasibility analysis (primary endpoint). Our primary hypothesis that the probability of completion is larger than 0.5 will be tested using a one-sided binomial test. Assuming *N* = 114 subjects, the one-sided binomial test would reject the null hypothesis (i.e., that the probability of completion is equal or less than 0.5) if the number of completers is ≥ 65 patients. This would constitute an effective completion rate of 57%. In terms of power, if the true completion rate is instead 2/3 (0.67), the probability of rejecting the null hypothesis would amount to approximately 0.98.

This sample size would also adequately power the efficacy analyzes (i.e., time x treatment interaction effect for MADRS change). Power in this analysis was estimated using a Monte-Carlo simulation of 10,000 datasets. Setting the threshold for detection at a significance level of 0.05 (one-sided), the estimated power for *N* = 114 subjects (38 enrolled per site) is 1-β = 0.91. A drop-out rate of 20% was incorporated, based on a comparable ongoing trial at the LMU Munich site [46]. Power measured the probability of detecting a significant time × treatment interaction effect. Effects were estimated using a linear mixed regression model (LMM), with time × treatment and center as fixed effects and subjects modeled as random effects. In the Monte-Carlo simulation, it was assumed that the time × treatment interaction effect was 4 points on the MADRS scale (adapted from [85]). The random effects were set at SD = 6 points for individual change (beyond baseline variability) and a standard deviation of 2.5 points was added as a center × treatment × time interaction. The assumed effect size of the interaction, after controlling for baseline, was Cohen’s *d* of 0.41 (medium effect size).

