Despite its strengths, the protocol of the DiSCoVeR trial has limitations that should be noted. First, the DiSCoVeR trial includes only two treatment arms: active vs. control. Given that each treatment arm includes a combination of two novel treatments (tDCS and video game), such a design will generate only preliminary proof-of-principle data of the combined treatment approach. Thus, little information will be generated regarding the effects of the separate treatment components of the combined therapeutic approach, independently of synergistic effects. In this sense, the DiSCoVeR trial will power a larger RCT, e.g., employing a 2 × 2 factorial or 4 arms design, which will allow a direct assessment of each of the treatment components in isolation. Second, since patients need to be instructed on how to operate the technology, some of the investigators including study operators, who do not conduct any study ratings, cannot be blinded. This is a common problem in studies involving behavioral interventions. To overcome any potential biases from investigators, raters in the DiSCoVeR trial remain blind to the treatment assignments of participants to avoid rater effects.

In sum, the DiSCoVeR trial could expand the range of treatment options for MDD by demonstrating the feasibility of this new neuromodulation enhanced intervention and by providing first data on the efficacy and safety of a novel home-based treatment for MDD with high scalability. Such a novel digital intervention could ultimately help overcome current barriers to mental health care, like low accessibility of non-digital psychotherapy and pharmacology treatment resistance, and represents a promising avenue toward guided, stratified or even personalized psychiatric care.

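### One published block size of four in each site × MADRS stratum makes about 30% of allocations certain to anyone who knows the earlier ones, which weakens concealment for the between-arm MADRS comparison

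*Protocol article*

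**What the plan says.** Under Randomization and blinding, the protocol article says that "Randomization is performed separately for each site", that patients are stratified by whether the MADRS is below or at least 21.5, and that "Within stratification, allocation is balanced in groups of four". Three sites and two MADRS groups make six separate lists. The Sample size calculation section plans 114 patients, "38 enrolled per site".

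The list itself is held away from the clinics: "Randomization is centrally performed by the coordinating site (HUJI) using an online randomization tool".

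On staff roles, the Study sites section says: "The three clinical trial sites are in charge of patient recruitment, patient screening, data assessment, and implementation of the intervention". Unblinded investigators and study operators deliver and supervise treatment at those sites. The Discussion accepts that "some of the investigators including study operators, who do not conduct any study ratings, cannot be blinded". Raters are separate personnel, blinded, and not in contact with patients during treatment sessions.

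**The concern.** A constant block size that is known lets an observer count. Once two patients in a block of four have received the same arm, the remaining two are known. Otherwise the fourth is always known. Holding the list centrally hides what has not yet been issued, but it does not hide what follows from allocations already seen. Unblinded treatment staff see the arm of each patient they treat. With two open blocks per site and an expected 2 to 3 patients per month per site, keeping track would be easy.

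The stake is selection. If someone who can foresee the next arm can also hasten, delay or decline an enrolment, patients with a better expected course could be steered to one arm. The comparison exposed is the group × time effect on the clinician-rated MADRS, together with the other between-arm comparisons. The efficacy model adjusts for baseline, sex and center. Selection on anything else, such as expected adherence or response, would remain.

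**Working it through.** The article gives no figure for predictability, so there is none to reproduce.

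**Inputs.** Block of four (Randomization and blinding). Two active and two control per block, inferred from the word balanced, because no ratio is written. Six lists (three sites × two MADRS groups). 38 patients per site (Sample size calculation). The split between MADRS groups is not given: 19 and 19 is assumed first, then all splits are checked. The observer is assumed to know all earlier allocations of the list in order.

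**One complete block.** There are six equally likely sequences. A position is certain when one arm is used up. The best guess is right with probability (larger remaining count)/(total remaining).

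| Position | Certain | Best guess right |
|---|---|---|
| 1 | 0 | 1/2 |
| 2 | 0 | 2/3 |
| 3 | 1/3 | 2/3 |
| 4 | 1 | 1 |

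- Certain: (0 + 0 + 1/3 + 1)/4 = 33.3%.
- Best guess: (1/2 + 2/3 + 2/3 + 1)/4 = 70.8%, against 50% without knowledge.

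**A list of 19** (four full blocks and three further positions).

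- Certain: (4 × 4/3 + 1/3)/19 = 5.667/19 = 29.8%.
- Best guess: (4 × 17/6 + 11/6)/19 = 13.167/19 = 69.3%.
- Over six lists: 6 × 5.667 = 34 of 114 allocations.

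**Any other split of 38.** The expected number certain per site is 11.33 or 12, so 29.8% to 31.6%, or 34 to 36 of 114. Best-guess accuracy is 69.3% to 70.2%. The unknown split hardly matters.

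**Varying block sizes.** 20,000 lists of 19 patients were simulated, with sizes drawn at random with equal probability. The observer knows the set of sizes and all past allocations, but not where blocks end. The count column is the share × 114.

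| Block sizes | Certain | Of 114 | Best guess right | Largest imbalance in a stratum |
|---|---|---|---|---|
| 4 only | 29.9% | 34 | 69.3% | 2 |
| 4 and 6 | 5.8% | 7 | 67.9% | 3 |
| 4, 6 and 8 | 2.3% | 3 | 66.6% | 4 |

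The fixed-block row agrees with the exact 29.8% and 69.3%. The largest imbalance is half the largest block.

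**Rater route.** If a rater learns one patient's arm and knows the block, the other three places hold one of that arm and two of the other. Each other member therefore moves from 1/2 to 2/3. In a block of six the figure would be 3/5.

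**The case against.** Four objections deserve weight.

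- **Nobody is shown to be able to use the prediction.** The article says that the sites recruit and screen, not that unblinded staff do. It says that some staff cannot be blinded, not that any one person follows all allocations in order and by stratum. It is a condensed article, and who decides enrolment is commonly set out in the full protocol or operating procedures. This stands: the harm is conditional, and the missing role description is not itself a fault. The fixed block size is different, because the article states it as the rule.
- **Blinding is not the problem.** A reader might infer that the block size undermines blinded rating. The documents do not support that. Those who can predict are unblinded by design and do no ratings, and they already know the arm of each patient they treat. Raters are kept apart from treatment sessions, and patients are asked not to discuss treatment with them apart from adverse events. A rater who did learn one arm would gain only a shift from 1/2 to 2/3 for the others in the block, and varying sizes would remove only part of that.
- **The primary endpoint is untouched.** Feasibility is tested in both arms together, so foreknowledge of the arm cannot create a between-arm bias there. This stands. The Discussion itself calls the data on the combined treatment preliminary proof of principle.
- **The remedy does little for guessing.** Best-guess accuracy falls only from 69% to 68% or 67%. This also stands. The gain lies in certain predictions, and certainty is what most readily supports deliberate timing of an enrolment.

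**Conclusion.** The point holds as a weakness in allocation concealment. With a single known block size of four, 33.3% of allocations in complete blocks, and 29.8% to 31.6% with 38 patients per site, can be deduced with certainty by someone who knows the earlier ones. The best guess is right about 69% to 71% of the time. This rests on 1:1 allocation within blocks and on an observer with full, ordered knowledge of a stratum. An observer who saw only part of the sequence would do worse.

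The consequence is conditional on such a person being able to influence whether or when a patient is enrolled. It concerns the between-arm comparisons, mainly the secondary MADRS analysis. A reader might conclude that a third of allocations were in fact foreseen, or that the efficacy result is biased. The documents support neither: they show an avoidable opportunity, not its use. Adjustment for baseline, sex and center would also absorb part of any selection, leaving what runs through unmeasured factors. The change is worth making because it is cheap and because selection of that kind cannot be repaired afterwards.

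**What to change.** For all allocations not yet made, replace the constant block of four with randomly varying block sizes within the same site × MADRS strata, for example 4 and 6, or 4, 6 and 8. Do not disclose the sizes to site staff. At 19 patients per stratum, certain predictions fall from about 30% to about 6% or 2%.

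The cost is a short amendment and a largest within-stratum imbalance of 3 or 4 patients instead of 2. That is minor, because baseline and center are in the efficacy model. Two things need to be established first: whether the online tool can change a list already in use, and how many allocations remain. The article gives neither, and the change does nothing for patients already randomized.

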### Sample size calculation

Sample size was determined based on the feasibility analysis (primary endpoint). Our primary hypothesis that the probability of completion is larger than 0.5 will be tested using a one-sided binomial test. Assuming *N* = 114 subjects, the one-sided binomial test would reject the null hypothesis (i.e., that the probability of completion is equal or less than 0.5) if the number of completers is ≥ 65 patients. This would constitute an effective completion rate of 57%. In terms of power, if the true completion rate is instead 2/3 (0.67), the probability of rejecting the null hypothesis would amount to approximately 0.98.

This sample size would also adequately power the efficacy analyzes (i.e., time x treatment interaction effect for MADRS change). Power in this analysis was estimated using a Monte-Carlo simulation of 10,000 datasets. Setting the threshold for detection at a significance level of 0.05 (one-sided), the estimated power for *N* = 114 subjects (38 enrolled per site) is 1-β = 0.91. A drop-out rate of 20% was incorporated, based on a comparable ongoing trial at the LMU Munich site [46]. Power measured the probability of detecting a significant time × treatment interaction effect. Effects were estimated using a linear mixed regression model (LMM), with time × treatment and center as fixed effects and subjects modeled as random effects. In the Monte-Carlo simulation, it was assumed that the time × treatment interaction effect was 4 points on the MADRS scale (adapted from [85]). The random effects were set at SD = 6 points for individual change (beyond baseline variability) and a standard deviation of 2.5 points was added as a center × treatment × time interaction. The assumed effect size of the interaction, after controlling for baseline, was Cohen’s *d* of 0.41 (medium effect size).

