### Statistical analysis

For the analysis of the primary endpoint (feasibility and completion rate), we will estimate the probability of completion using the Binomial Fisher’s Exact Test, assuming individuals across centers are independent. Letting *P* be the probability of successful completion (week 6), we will reject the null hypothesis that *P*_(completion)_ ≤ 0.5. A confidence interval for *P*_(completion)_ will be estimated. In a second step, we will estimate the confidence intervals for each of the treatment arms separately.

The analysis of the secondary endpoint (efficacy) consists of an intention-to-treat (ITT) analysis of the change in MADRS scores from baseline to post-intervention by adjusting for inter-individual differences at baseline, sex, and center. A linear mixed regression model (LMM) with random intercepts and center, group, time, and the cross-level group x time interaction as fixed effects will be performed. The key value for significance will be the group × time interaction factor. In case of significant group × time interactions, post-hoc comparisons at each time point with correction of the type-I error probability will be conducted. Confidence intervals for mean differences and effect sizes will be computed. If the analysis at week 6 is found to be significant, an analysis of change over 10 weeks will be performed as a final analysis step concerning the secondary endpoint. All tertiary endpoints will be similarly analyzed using LMMs. Logistic regression will be used to analyze discrete tertiary endpoints (i.e., response and remission rates).

There will be no imputation in the ITT analyzes as the LMMs can handle missing values without excluding entire cases from the analysis. As a sensitivity analysis, LMMs can be computed using state-of-the-art multiple imputation of missing values. At 50% of subjects having completed the study, a planned interim analysis will assess safety and feasibility outcomes. The respective results will be shared with our SMB and published, but will not impact on the conduct of the study, unless major ethical concerns arise.

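### The critical count printed for the primary feasibility test (65 of 114) does not match one-sided 5% or 2.5%, and no significance level is stated for that test

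*Protocol article*

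**What the plan says.** The primary endpoint is feasibility, judged by whether the probability of completing at least 20 of 30 sessions exceeds 50%, with both arms pooled (Study endpoints).

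The Sample size calculation section says that this hypothesis "will be tested using a one-sided binomial test". With 114 subjects the test "would reject the null hypothesis (i.e., that the probability of completion is equal or less than 0.5) if the number of completers is" 65 or more. The text continues: "This would constitute an effective completion rate of 57" per cent. On power it says: "if the true completion rate is instead 2/3 (0.67), the probability of rejecting the null hypothesis would amount to approximately 0.98". No significance level is attached to this test. A level of 0.05 (one-sided) appears in the next paragraph, for the simulated power of the MADRS analysis.

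The Statistical analysis section gives no critical count. It plans an exact test of the same null hypothesis, "assuming individuals across centers are independent", and a confidence interval for the completion probability, without a level or side. It labels the test with both the binomial and Fisher's name.

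**The concern.** Sample size, null value, sidedness and rejection count are all printed, so the size of the rule can be computed exactly. A critical count is correct only for a given alpha, and 65 looks too low for 114 subjects at the usual levels.

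The count marks the boundary between feasible and not feasible on the primary endpoint. If it is too low, the article holds two rules that disagree for some outcomes: the printed count, and the exact test that the analysis section says will be run. A reader holding 65 or 66 completers could not tell from the document whether the primary hypothesis had been met.

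**Working it through.** **Inputs**

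- N = 114, both arms pooled (Sample size calculation; Study endpoints).
- Null value p0 = 0.5, one-sided test (Sample size calculation).
- Printed rule: reject at 65 or more completers; 65/114 = 57.0%, which agrees with the printed 57%.
- Alternative p1 = 2/3, stated power about 0.98 (Sample size calculation).
- Alpha: not given for this test. I take one-sided 0.05 from the efficacy paragraph as an assumption and also show 0.025 and 0.10.

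**Formula**

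For a rule that rejects at r or more completers:

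- Size = P(X ≥ r | n = 114, p = 0.5) = Σ C(114, k) · 0.5^114, for k = r to 114.
- Power = P(X ≥ r | n = 114, p = 2/3).

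**The plan's own power figure**

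For 65 or more, power at 2/3 is 0.988 (0.990 at 0.67). This is within one percentage point of the stated 0.98, so the power statement is reproduced to the accuracy claimed.

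**The plan's critical count**

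| Reject at | Rate | Exact size at 0.5 | Power at 2/3 |
|---|---|---|---|
| 65 or more | 57.0% | 0.0799 | 0.988 |
| 66 or more | 57.9% | 0.0555 | 0.980 |
| 67 or more | 58.8% | 0.0373 | 0.969 |
| 68 or more | 59.6% | 0.0244 | 0.953 |

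The smallest valid count is 65 at one-sided 0.10, 67 at 0.05 and 68 at 0.025. The printed 65 fits only 0.10, a level the document never states.

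**Does another version of the test give 65 at 5%?**

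Under p = 0.5 the mean is 57 and the variance is 114 × 0.25 = 28.5. For 65 completers:

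- Normal approximation: z = (65 − 57)/√28.5 = 1.50, p = 0.067.
- With continuity correction: (64.5 − 57)/√28.5, p = 0.080.
- Wald: p = 0.065.
- Mid-p: p = 0.068.
- Reading the rule as strictly more than 65: p = 0.0555.

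None reaches 0.05. For 66 completers the uncorrected normal (0.046), Wald (0.044) and mid-p (0.046) versions do, but the analysis section names an exact test, and there 66 gives 0.0555.

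**Confidence limits**

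Exact (Clopper-Pearson) lower limits:

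- One-sided 95%: 0.489 at 65, 0.498 at 66, 0.506 at 67.
- Two-sided 95%: 0.492 at 67, 0.5005 at 68.

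The one-sided 95% limit clears 0.5 from 67, as the one-sided 5% test does. The two-sided 95% interval clears it only from 68, as the 2.5% test does.

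**Dependence on the final N**

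At one-sided 0.05 the exact critical count is 65 for N = 110 or 111, 66 for N = 112 or 113, and 67 for N = 114.

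**The case against.** The strongest reply is that 5% is inferred. The document attaches no alpha to the feasibility test, and 65 is the exact threshold at one-sided 10%. This stands as a limit on the claim: the supportable statement is that 65 fits neither the only level the document gives nor 0.025. It does not rescue the text. A 10% test of the primary endpoint beside a 5% test of the secondary one would have to be stated.

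The second reply is that 65 appears in the sample size section as a consequence of the test, while the analysis section sets no count. This also stands. A reader might infer that the trial will run its primary test at an 8% false-positive rate, or will declare success at 65 or 66. The document does not support that. The 8.0% arises only if 65 is used as a literal cut-off; the exact test run at 5% gives p = 0.080 at 65 and does not reject. What is shown is a wrong printed critical count that conflicts with the planned test.

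Third, a reader might infer that the planned confidence interval will contradict a success at 65 or 66 but agree with one at 67. That holds only for a one-sided 95% limit. With a two-sided 95% interval, 67 also includes 0.5. The article fixes neither level nor side.

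Fourth, the stated power of about 0.98 equals the value for 66 to three decimals, but 0.988 is close enough to an approximate 0.98 that nothing can be concluded about how the figure was obtained. The Fisher label is a naming slip: a single pooled proportion tested against 0.5 can only be the one-sample binomial test.

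Finally, the practical effect is small if the planning assumption is right. At a true rate of 2/3 the chance of exactly 65 or 66 completers is 0.9877 − 0.9688 = 0.019. This bears on likelihood, not on whether the printed count is correct.

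**Conclusion.** The point holds as a wrong critical count for the primary test together with a missing alpha. With N = 114 and p0 = 0.5, rejecting at 65 or more has exact size 0.080, above both 0.05 and 0.025. If one-sided 5% is meant, the count is two patients too low, and 65 and 66 completers are the outcomes on which the printed rule and the planned exact test disagree. The choice of 5% is an assumption carried over from the efficacy paragraph; the sizes themselves rest only on printed figures and on independent participants, which the article also assumes.

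The sample size is not in question: power at 2/3 stays at about 0.97 with 67 and about 0.95 with 68. Because the count decides the primary endpoint, it should be corrected before the primary analysis is carried out.

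**What to change.** State alpha for the primary test and print the count that matches it:

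- One-sided 0.05: reject at 67 or more of 114 (58.8%); exact alpha 0.037; power about 0.97 at a true rate of 2/3.
- One-sided 0.025: reject at 68 or more of 114 (59.6%); exact alpha 0.024; power about 0.95.

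If 65 is to be kept, one-sided 0.10 has to be declared and justified.

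Add that the critical count is recomputed from the exact binomial distribution if the number analysed is not 114. Report a Clopper-Pearson interval at the level and side that match the test, so that interval and test cannot disagree. As a minor edit, call the test in the Statistical analysis section the exact one-sample binomial test.

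The cost is wording only. The count rises by two or three patients, power at 2/3 falls from 0.988 to 0.969 or 0.953, and recruitment is unchanged.
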